##### Analysis plan for economic data

Service costs will be calculated by combining the service use data with appropriate local unit costs. Cost comparisons will be made using bootstrapping methods to account for skewed data. Cost-effectiveness will be assessed by combining costs with outcomes in the form of incremental cost-effectiveness ratios which will show the extra cost incurred (if any) to produce a unit improvement in the main outcomes (symptoms and disability) as well as QALYs (measured using the EQ-5D combined with appropriate utility weights). Uncertainty around cost-effectiveness estimates will be explored using cost-effectiveness planes and interpretation will be aided using cost-effectiveness acceptability curves.

##### Analyses plan of qualitative data

Analyses of interview data will commence as data collection is ongoing and will involve importing interview transcripts into qualitative analysis software (NVivo8) for coding and identification of key themes. Analyses of the baseline qualitative data will explore illness experiences of people with schizophrenia and their caregivers, with a particular focus on experiences of stigma and discrimination.

As part of the 12-month follow-up qualitative analyses, treatment arms will be compared with regards to themes such as the impact of the illness on persons with schizophrenia and caregivers including experiences of stigma and discrimination, met and unmet needs and other themes that emerge as important from the data. There will also be a focus on understanding the experiences of care received, including their acceptability and perceived effect, perceptions of interactions with staff and attributions of changes from entry into the trial to endpoint. Examples of possible unintended or even negative consequences of CCBC will be sought out. Staff interviews will concentrate on staff's perspectives on the impact of the intervention on the study outcomes.

##### Trial management and monitoring

The COPSI study will be conducted according to the good clinical practice guidelines recommended for conducting multi site randomized controlled trials. There will be a dedicated Trial Coordinator who will coordinate the recruitment and progress of the trial in conjunction with each of the site Project Management Committees set up for this purpose.

##### Ethical considerations

Even though there is observational evidence from uncontrolled studies about the effectiveness of community based interventions, there is genuine clinical equipoise regarding the question of the effectiveness and affordability of community care in Low and Middle Income Countries (LAMIC). This trial is justified in this context of paucity of evidence from such contexts, derived from rigorous controlled studies, about the clinical and cost effectiveness of community services for people with schizophrenia.

Underpowered trials are unethical and we have made provisions to have adequate power in the COPSI study. We have calculated the sample size in a systematic fashion at several levels. This includes having a threshold of 95% power (using alpha = 0.05) for detecting a clinically significant difference in the primary outcome measure between the two arms. We have also specifically addressed the issue of clustering effects within treatment sites and CHWs delivering the intervention in calculating our sample size. Based on these assumptions, we feel the study is adequately powered to detect differences in a robust manner to generate valid results.

We will ensure that the rights of participants are protected during the conduct of the trial in accordance with good practice ethical obligations. To address the problems associated with obtaining consent from people with schizophrenia who are symptomatic and sometimes non-literate, the consent procedure will be carried out using non technical language and, in a manner designed to enhance the intake and retention of information. This includes the use of a specially designed flipchart illustrating the key components of the information relevant to informed decision making. Irrespective of the decision to participate or not, no person with schizophrenia will be deprived of any treatment s/he will ordinarily receive. Participants will be free to withdraw from the study at any stage without compromising their usual clinical care. Finally, informed consent to participate in the trial will be recorded by using a form that is in compliance with the Helsinki Declaration and Good Clinical Practice (GCP) guidelines[29]; these have been approved by regulatory bodies.

Arrangements will be made to comply with suggested GCP guidelines in related to protecting the confidentiality of personal data principally through procedures to separate study data and participant identifiable data. For the quantitative data, the data gathered in the palmtops for each participant and the family at baseline will be checked by the Data Manager who will remove all personal identification items (to be kept as a separate file with restricted password protected access to the Data Manager only) and assign a unique Trial ID. All future data will be collected and collated using only the ID number. Regarding the qualitative data set, participant and caregiver files will be kept in locked cabinets with only the interviewers and the research coordinator having access. All identifying information (i.e. name, socio-demographic data etc) will be removed from the interview data and kept separately. Both the individuals and caregivers will be given unique ID codes (i.e. not having name/any other identifying information). Soft copies of transcriptions will be kept in password protected files in a secure computer. Transcriptions will have no identifying information.

Formal ethical approval for conducting the trial has been sought and obtained from the ethics committees at the Kings' College, London (PNM/08/09-121), the London School of Hygiene and Tropical Medicine (approval number 5579) and from the respective Institutional Review Boards at SCARF and Sangath. The trial is registered with the International Society for the Registration of Clinical Trials and the allocated unique ID number is ISRCTN 56877013.

The trial will be regulated by an independent Trial Monitoring Committee (TMC) represented by experts and user representatives who have reviewed and formally approved the protocol before commencing recruitment. The TMC will be provided with quarterly updates describing the trial progress during the recruitment period and every 6 months thereafter. A *critical incident register *will be maintained during the study to record four specific serious adverse events- death, suicide attempt, hospitalization (from any cause) and serious medication side effects like neuroleptic malignant syndrome, tardive dyskinesia, akathisia and tremors for participants in both arms of the study; these are in accordance with the recommendations of the TMC. Across both arms, these adverse events will be recorded by the treating Psychiatrists as they occur and by the researchers who will be collecting quantitative data at 6 and 12 months. For participants in the CCBC arm, the concerned CHW will also report these events. The reporting and per protocol action taken for each adverse event will be made available the TMC during the updates. The TMC is also empowered to independently review the ethical and data management procedures of the trial as per established good practice norms.

The TMC can examine the unblinded outcome and adverse event data during the planned annual review meetings and will be consulted before the public reporting of the results of the study. Updates will be provided to all concerned ethics committees of major changes in the protocol, if necessary.

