• *structured psycho-educational information *about various issues related to the understanding and proactive management of the illness for the participant and the care givers as well as specific efforts to identify and address experiences of stigma and discrimination

• *adherence management *strategies to reduce the rates of non-adherence to treatments

• *health promotion strategies *to improve the physical health status of people with schizophrenia

• Specific *rehabilitation strategies *to improve the personal, social and vocational functioning of participants

• Linkage to *self help groups *and other methods of user led support

• Developing *networks with community agencies *to address social problems in the family like poverty or interpersonal disputes and facilitate a supportive framework for participants to seek employment and access to social and legal benefits

The intervention is delivered in three phases. In the initial, 3 month *intensive engagement phase*, the key tasks will include developing a positive therapeutic alliance with the person with schizophrenia and care givers, conducting the needs assessment and generating the collaborative individual treatment plan. There will also be a focus on identifying and addressing familial social difficulties that have an adverse impact on the person with schizophrenia, adherence management and structured psycho-education sessions. We anticipate that CHWs will conduct 6-8 home based (or other convenient location nominated by the person and care givers) sessions during this phase.

In the second, *stabilization phase *during months 4-7, the CHWs will conduct a total of 6-8 fortnightly sessions. In this phase, the focus will be on addressing the unmet or partially met needs from the first phase, reinforce psycho-education and adherence, and introduce other components like health promotion, rehabilitation needs assessment and interventions (for example, improving activities of daily living skills and social skills training), and improving social interactions within and outside of the family.

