In the final, *maintenance phase *during months 8-12, the CHWs will conduct 6 sessions. In this phase we intend to reinforce the progress made, discuss strategies to deal with distressing symptoms, discuss ways of dealing with experiences of stigma and discrimination, focus on restoration of social and economic roles, generate a relapse prevention plan and address remaining unmet needs, to the extent possible before a carefully planned termination.

In total, we anticipate that each participant in the CCBC arm will receive a maximum of 22 planned contacts during the 12 months of the intervention, and that each CHW will carry a maximum case load of 25 people with schizophrenia at any one time. In evaluating the intervention, we have set an a priori definition of 'minimum adequate' as being 12 sessions of the CCBC sessions delivered over 12 months.

All informational materials meant for the use of participants and caregivers has been systematically translated into the five regional languages used across the trial sites. The intervention has been systematically piloted at each of the sites. Based on the results of the field testing, the final content and process of the phase specific delivery of the intervention has been manualised, as mentioned earlier.

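### The critical incident register has an extra reporter, the CHW, in the CCBC arm only, so its by-arm counts are open to detection bias against CCBC, mainly for suicide attempts and side effects.

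*Protocol article*

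**What the plan says.** Under Ethical considerations, the protocol article sets up a critical incident register for four kinds of event: "death, suicide attempt, hospitalization (from any cause) and serious medication side effects like neuroleptic malignant syndrome, tardive dyskinesia, akathisia and tremors". Two sources are common to the arms: "Across both arms, these adverse events will be recorded by the treating Psychiatrists as they occur and by the researchers" who interview at 6 and 12 months. The next sentence adds a source in one arm: "For participants in the CCBC arm, the concerned CHW will also report these events".

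The section on the CCBC intervention shows how often that source is present. In the engagement phase, "We anticipate that CHWs will conduct 6-8 home based" or similarly located sessions; in the stabilization phase, "the CHWs will conduct a total of 6-8 fortnightly sessions"; and "during months 8-12, the CHWs will conduct 6 sessions". The stated total is that "each participant in the CCBC arm will receive a maximum of 22 planned contacts during the 12 months of the intervention".

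Register reports go to the Trial Monitoring Committee (TMC) at its regular updates, and the TMC may examine adverse event data unblinded at its annual reviews. Table 2 separately lists inpatient stay, taken from the treating psychiatrist's records, and serious medication side effects, taken from those records and the 6- and 12-month assessments. Neither entry names the CHW.

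**The concern.** A count of adverse events depends on how many occur and how many are found. Here the second factor differs by arm by design. Under Facility based Care, clinically stable patients may see the psychiatrist only every one to three months, and the researchers call twice after baseline. In the CCBC arm the CHW may be the most frequent observer, often at home.

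The events most exposed are those that a clinic visit or a six-monthly interview can miss: a suicide attempt that never reached care, or akathisia and tremors that were not mentioned. If the TMC compares register counts by arm, or the final report tabulates them, equal true risks can look like an excess under CCBC, and a modest true reduction could be partly hidden. No formal test is needed for this to matter, because an unblinded committee reading unequal counts may react to them.

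**Working it through.** **Contacts.** The plan's figure reproduces. The phase maxima give 8 + 8 + 6 = 22, and the minima give 6 + 6 + 6 = 18.

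**Sources by arm.**

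| Source | CCBC | FBC |
|---|---|---|
| Treating psychiatrist, as events occur | yes | yes |
| Researcher, at 6 and 12 months | yes | yes |
| CHW | yes | no |

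**Size of the distortion.** Let s be the chance that the common sources catch an event, taken as equal in the two arms, and c the chance that the CHW catches an event they missed. The article gives neither value and no event rate, so all of these are assumptions. With equal true risk, the recorded CCBC:FBC ratio is

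[s + c(1 − s)] / s.

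With c = 0.5:

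- s = 0.95: 0.975 / 0.95 = 1.03
- s = 0.80: 0.90 / 0.80 = 1.13
- s = 0.60: 0.80 / 0.60 = 1.33

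Varying c as well:

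| s | c = 0.25 | c = 0.5 | c = 0.8 |
|---|---|---|---|
| 0.60 | 1.17 | 1.33 | 1.53 |
| 0.80 | 1.06 | 1.13 | 1.20 |
| 0.95 | 1.01 | 1.03 | 1.04 |
| 1.00 | 1.00 | 1.00 | 1.00 |

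The ratio is never below 1. Deaths and most admissions belong near the bottom rows; unreported suicide attempts and milder side effects belong nearer the top.

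**What a reader of the counts would see.** Take 188 CCBC and 94 FBC participants (Sample size estimation), an assumed true risk of 20% in both arms, and c = 0.5. At s = 0.80 the expected recorded counts are 94 × 0.20 × 0.80 = 15.0 for FBC and 188 × 0.20 × 0.90 = 33.8 for CCBC. Equal ascertainment would give 188 × 0.20 × 0.80 = 30.1 for CCBC. By normal approximation, the chance of a nominal two-sided 5% result against CCBC is 3.1% at s = 0.95, 5.9% at s = 0.80 and 13.3% at s = 0.60, compared with 2.5% when there is no bias. At an assumed risk of 5%, the corresponding figures are 2.7%, 3.6% and 5.4%.

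**Effect of restricting to common sources.** Counting only events that the psychiatrist or researcher recorded gives s / s = 1.00 for every s, provided CHW information does not enter the psychiatrists' records.

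**Why the first source alone is not enough.** If the register kept only the first reporter and CHW-first events were dropped, CCBC would lose events that a common source also recorded. If the CHW is first on a fraction f of those, the ratio under equal risk becomes 1 − f, for example 0.70 at f = 0.3. That reverses the bias and could hide harm.

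**The case against.** The strongest reply is that the article plans no formal between-arm test of register events. They appear in neither the objectives nor Data management and analysis, and the register is described as a monitoring tool. How the TMC or final safety tables are built is normally left to an analysis plan, operating procedure or committee charter that is not shown. The article also does not list the register's fields, so the reporter may already be recorded. This stands: the text supports a risk of distorted counts, not a planned biased estimate, and silence on table layout is not the fault. What remains is the stated reporting rule, which makes ascertainment unequal whatever tables follow.

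A reader might infer that comparisons of all four event types are biased alike, and that a real benefit on admissions would be masked. The documents do not support that. Deaths and most admissions should reach the psychiatrist, or be found when researchers interview participants and caregivers. Table 2 takes inpatient stay and serious side effects from sources named identically for both arms. Two limits apply to this reply. Table 2 does not list suicide attempts. And its sources are not fully insulated, because CHWs have scheduled meetings with the psychiatrists, who are unblinded.

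**Conclusion.** The point holds as a risk of detection bias against CCBC in by-arm register counts. The direction follows from the reporting rule as written, provided CHW reporting does not displace recording by the psychiatrist or researcher. The size is unknown: with c = 0.5 it runs from about 1.03 at 95% common-source capture to 1.33 at 60%, and both capture rates are assumptions. It is likely small for deaths and admissions and matters mainly for suicide attempts not brought to care and for side effects such as akathisia and tremors. The primary outcomes and Table 2's inpatient and side-effect measures do not use the CHW as a named source. This is worth correcting because it is cheap and because source information is hard to reconstruct later.

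**What to change.** - Keep CHW reporting for the safety of individual participants.
- On the register, record every source that reported each event (psychiatrist, researcher, CHW), not only the first.
- Base any between-arm comparison, for the TMC or the final report, on events recorded by the psychiatrist or researcher, whether or not the CHW also reported them.
- Show CHW-only events separately, beside the all-source totals, so that no event is hidden.

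The cost is one multi-source field and one extra table. The common-source comparison leaves out a few genuine CCBC events, which remain listed. Some bias will persist, because what the CHW learns can reach the psychiatrist's own records through their scheduled meetings; the safety table should carry a note saying so.

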## Discussion

Providing community based services for greater numbers of people with schizophrenia in low and middle income countries is an urgent public health priority. The COPSI randomized controlled trial builds on previous observational evidence of the feasibility, acceptability and effectiveness of CBR programs that incorporated lay community health workers as the front line service providers. This trial is designed to provide quality evidence about the clinical effectiveness of the intervention and the economic implications of the community intervention.

Given the 'real life' sample of subjects and the diversity of the sites where the study will be conducted, we believe that the results of the study will be generalisable beyond the study population. If the results confirm the hypotheses and CCBC intervention has additional clinical benefits and is cost effective, this can have significant impact on health policy related to the scaling up community care for people with schizophrenia in India and other LAMIC. The results of the trial will be used to inform policy makers and practitioners about the benefits, necessary human resources and costs of a community based intervention that can be fronted by non-specialist workers (working in tandem with specialists), involve the person with schizophrenia and the family and engage proactively with the local community in promoting recovery and social inclusion.

Finally, through the detailed exploration of experiences of stigma and discrimination and evaluation of the intervention on stigma outcomes, the study will also contribute to the limited evidence on felt experiences and effective interventions to reduce stigma and discrimination for people with severe mental disorders in LAMIC.
